### Study interventions

#### Anesthesia preparation stage

All children are screened for eligibility by an experienced anesthesia assistant who will not be involved in block sizes and future allocation. Baseline data including heart rate (HR), systolic blood pressure (SBP), diastolic blood pressure (DBP), pulse oxygen saturation (SpO_2_) are recorded. Children with a diagnosis of pneumonia or airway foreign body but with a stable, improving, or predictable pattern of cough will be eligible for inclusion. Their baseline cough frequency (“occasional” or “frequent but stable”) will be recorded as a characteristic for group comparison. Children are restricted from consuming solid foods for 6 h and clear fluids for 2 h prior to undergoing FFB (26). A patent intravenous cannula is inserted, and premedication with intravenous midazolam at a dose of 0.05 mg⋅kg^–1^ is given in the ward. Topical anesthesia is achieved by administering a 2-milliliter nebulized 2% lidocaine solution through inhalation before the procedure in the ward.

#### Anesthesia induction stage

All FFB procedures are carried out in the outpatient bronchoscopy room with children positioned in a supine position. Throughout the procedures, HR, end-tidal partial pressure of carbon dioxide (PetCO_2_), SpO_2_, body temperature and the bispectral index (BIS) are continuously monitored and noninvasive blood pressure (NIBP) is measured at 3-min intervals. Anesthesia depth is monitored using a combination of standard clinical signs and BIS. The BIS is a dimensionless number ranging from 0 to 100, which is calculated based on frontal electroencephalographic signals. The primary goal is maintaining clinical signs of adequate anesthesia, defined by the absence of purposeful movement or gross sympathetic response (tachycardia > 20% above baseline or hypertension > 20% above baseline). The BIS value of 40–60 serves as a secondary guide, which is intended as an adjunctive, quantitative tool to minimize the risk of awareness and help maintain a relatively stable hypnotic state. A nasopharyngeal temperature probe is promptly placed after the induction of anesthesia, and temperature readings are documented at 3-min intervals throughout the entire case. Normothermia is precisely defined as a core temperature ranging from 36.0 °C to 37.5 °C. To effectively maintain normothermia, a forced-air warming blanket that is set at a temperature between 32 °C and 43 °C is available if needed. In the event that body temperature falls below 36.0 °C, the forced-air warmer temperature is increased. No patient is discharged from the operating room with a body temperature < 35.5 °C. TOF ratio is monitored immediately prior to the insertion of LMA and upon the completion of the procedure. All participants receive anesthesia that is administered by the same primary anesthesiologist. Following the intravenous administration of propofol at a dosage of 3 mg⋅kg^–1^, TOF stimulation is delivered at 15-s intervals. After 2 min of stable readings, the baseline twitch height is set to 100% for calibration. Then, remifentanil is administered at a dosage of 3 μg⋅kg^–1^. As spontaneous breathing gradually subsides, manual mask ventilation with 100% oxygen is provided as a supportive measure. Subsequently, an intravenous dosage of rocuronium at 0.3 mg⋅kg^–1^ is administered to the rocuronium group, while an equivalent volume of normal saline is given to the normal saline group. Immediately after the administration of all the induction drugs, remifentanil is infused at an initial rate of 0.05 μg⋅kg^–1^⋅min^–1^ (7). After 60 s of the administration of rocuronium or normal saline, the TOF ratio is recorded, and an appropriately sized LMA is inserted. The LMA is then connected to an anesthesia machine to manage ventilation in synchronized intermittent mandatory ventilation mode with a tidal volume of 6 ml/kg and adjust the breathing rate to maintain PetCO_2_ at 30–40 mmHg. Oxygen is delivered at a concentration of 50% and a flow rate of 2 L/min. Meanwhile, sevoflurane is titrated with an initial concentration of 1.5% through the LMA to maintain the appropriate anesthesia depth. If the clinical signs are adequate but the BIS values persistently exceed 60, the concentration of sevoflurane is increased in 0.5% increments. Conversely, if the BIS values are within or below the target range but the clinical signs suggest light anesthesia (such as movement, tachycardia or hypertension), the clinical signs take precedence, and the concentration of sevoflurane is increased in 0.5% increments. No reduction in the sevoflurane concentration is made solely based on a low BIS value if the clinical assessment indicates an adequate depth of anesthesia.

#### During the procedure

An Olympus BF-XP290 flexible fiberoptic bronchoscope with an outer diameter of 2.8 mm, or a BF-P290 with an outer diameter of 4.0 mm is inserted through the bronchoscope connector. The suction port is sealed with a Polyvinyl Chloride cover to create an airtight seal around the bronchoscope. When the vocal cords are visualized, 2% lidocaine, usually administered in a volume of 1 mL, is applied to the vocal cords via the bronchoscope to prevent laryngospasm. Then, the vocal cords are carefully traversed, and 1 ml of 2% lidocaine is instilled into the tracheobronchial tree using the “spray as you go” technique (27). Further diagnosis and treatment of the airway using a flexible bronchoscope is performed based on the specific clinical context. The infusion rate of remifentanil is adjusted every minute, increasing or decreasing by 0.01 μg⋅kg^–1^⋅min^–1^ based on any signs of coughing. If a cough reaction occurs, the infusion rate is increased; if no cough reaction is observed, the infusion rate is decreased, as determined by the primary anesthesiologist. Supplemental boluses of 1–2 μg⋅kg^–1^ remifentanil will be administered as a remedy and repeated as needed in the event of persistent coughing. If blood pressure or other hemodynamic parameters preclude the administration of adequate doses of remifentanil, a supplementary dose of rocuronium (0.2 mg⋅kg^–1^) is administered. Cases in which a supplementary dose of rocuronium is administered are defined as those “with the highest incidence of coughing” and are categorized as “failure cases.”

#### Anesthesia recovery stage

Upon completion of the procedure, discontinue all medications. Remove the LMA once spontaneous breathing has fully recovered and the TOF ratio reaches 0.9. Although the protocol employs a low dose of rocuronium, and spontaneous recovery to a TOF ratio ≥ 0.9 is anticipated within 20–30 min in most children, sugammadex is readily available and will be administered at the end of the procedure if the TOF ratio remains <0.9 or if there are clinical signs of residual neuromuscular blockade such as inadequate tidal volume. The decision to reverse is made by the primary anesthesiologist. The dose of sugammadex will be 2 mg⋅kg^–1^ if the TOF ratio is <0.9, a dose sufficient for rapid reversal of low-dose rocuronium-induced moderate neuromuscular blockade while avoiding unnecessary higher-dose exposure. If spontaneous recovery has already achieved a TOF ratio ≥ 0.9, no reversal agent will be given. The usage, dosage and the corresponding TOF ratio at the time of reversal will be recorded. Following the removal of the LMA, children will be transferred to the post-anesthesia care unit (PACU). Hemodynamic data (HR, SBP, DBP), SpO_2_ and coughing scores are monitored every 5 min until children are discharged. Coughing scores is defined according to the frequency of coughing episodes: Grade 0 (no coughing), Grade 1 (minimal: once or twice), Grade 2 (moderate: 3–4 times), and Grade 3 (severe: 5 or more times). Children are ready for discharge when they are fully awake and have reached a modified Aldrete score of ≥9.

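### The recovery section gives opposite instructions on sugammadex for a child who has had rocuronium and shows clinical signs of residual block at a TOF ratio of at least 0.9

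*Protocol article*

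**What the plan says.** All the relevant text stands in one paragraph of the protocol article, under Anesthesia recovery stage.

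- **Instruction to reverse.** It says that "sugammadex is readily available and will be administered at the end of the procedure" on either of two conditions: "if the TOF ratio remains <0.9 or if there are clinical signs of residual neuromuscular blockade such as inadequate tidal volume".
- **Who decides.** "The decision to reverse is made by the primary anesthesiologist".
- **Dose.** The single stated dose carries one condition, the TOF trigger: "if the TOF ratio is <0.9, a dose sufficient for rapid reversal".
- **Instruction not to reverse.** "If spontaneous recovery has already achieved a TOF ratio ≥ 0.9, no reversal agent will be given". The operative words, "no reversal agent will be given", carry no exception for clinical signs.
- **LMA removal.** "Remove the LMA once spontaneous breathing has fully recovered and the TOF ratio reaches 0.9".

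The paragraph also says that sugammadex use, its dose and the TOF ratio at reversal are recorded. No other section returns to the question of which sentence governs when the TOF ratio and the clinical signs disagree.

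**The concern.** The two triggers for reversal are joined by an unconditional *or*, so clinical signs of residual block are sufficient on their own. The later sentence forbids reversal on the TOF ratio alone. Where the ratio has reached 0.9 and signs are present, the plan both requires and forbids the same drug.

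This is a rule for children aged 1 to 6 years recovering from anesthesia, so a contradiction matters even if it is seldom met. It also has a modest statistical side. Discharge time, a secondary endpoint, runs from removal of the bronchoscope to a modified Aldrete score of at least 9, and the reversal decision falls inside that interval. A per-protocol analysis is planned, and in the disputed case either action can be called a deviation.

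**Working it through.** No sample size, power or event figure enters this point, so the check is one of logic. Call the instruction to reverse rule A and the instruction not to reverse rule B, and apply both to each combination of TOF ratio and clinical signs in a child who has had rocuronium.

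| TOF ratio | Clinical signs of residual block | Rule A | Rule B | Result |
|---|---|---|---|---|
| <0.9 | present | give | silent | consistent |
| <0.9 | absent | give | silent | consistent |
| ≥0.9 | absent | silent | do not give | consistent |
| ≥0.9 | present | give | do not give | contradictory |

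1. Three of the four cells are consistent and one is not.
2. Below 0.9 the TOF trigger already calls for reversal, so the clinical-signs trigger changes nothing there. The only cell in which it adds anything is the fourth, and that is the cell in which rule B forbids reversal. As written, rule B cancels the whole effect of the clause "or if there are clinical signs of residual neuromuscular blockade such as inadequate tidal volume". Either that clause is empty or rule B lacks an exception, and both readings call for an edit.
3. The dose sentence is conditional on a ratio below 0.9. It matches rule B and leaves the signs-only trigger of rule A without a dose.
4. The text does not treat the fourth cell as impossible. Rule A lists clinical signs as an alternative to a low ratio, and the LMA rule names recovered breathing and a TOF ratio of 0.9 as two separate conditions.
5. The article does set precedence where it has thought of it: under Anesthesia induction stage, clinical signs prevail over the bispectral index when the two disagree. There is no such statement for the TOF ratio.
6. The children concerned are those given rocuronium. That means the rocuronium group, and also any saline-group child given the supplementary dose described under During the procedure, which is not limited to one group.

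**The case against.** The strongest reply is that the consequence is limited, and most of that reply stands.

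- **The anesthesiologist decides.** This softens the conflict in practice. It does not remove it, because both rules are worded as firm and neither is subordinate to the other. According to Anesthesia induction stage, the same primary anesthesiologist treats every participant, so variation between clinicians is not an issue.
- **Rule B may be meant only as the complement of the TOF trigger.** That is possible, but the sentence does not say so, and on that reading it still needs an exception.
- **An article may leave detail to the full protocol.** This is fair for a bare omission. Here both rules are printed, and they conflict. The dose sentence matters only because it has to agree with whichever rule is kept.

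A reader might also infer four stronger things that the document does not support.

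- **That saline-only children with low tidal volume meet rule A.** The trigger is signs of residual neuromuscular block, with low tidal volume as an example. A child who has had no rocuronium has no such block, and the primary anesthetist is unblinded and knows this (Randomization and blinding).
- **That the conflict will be frequent.** The article expects spontaneous recovery within 20–30 min in most children, and the Statistical analysis section cuts a subgroup at 20 min. Neither figure forecasts TOF values at the end of the procedure. A ratio near 0.9 is also not the conflict: only a ratio of at least 0.9 together with signs is.
- **That the airway could come out too early.** The removal rule requires both conditions, so a child with inadequate breathing does not meet it under either sugammadex sentence.
- **That discharge time will be biased by arm.** The decision-maker knows the allocation, so this is conceivable, but nothing in the document shows that it would happen or how large it would be.

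**Conclusion.** The contradiction is real and confined to one case: a child who has received rocuronium, has recovered spontaneously to a TOF ratio of at least 0.9, and shows clinical signs of residual block. For that child the paragraph gives opposite instructions and states no dose.

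The number affected cannot be computed from the document. That it is small is a judgement, resting on the need for two findings to coincide that would usually point in different directions. The primary endpoint, coughing episodes per unit of procedure time, is complete when the bronchoscope is removed and so before the reversal decision. Of the ten secondary endpoints only discharge time is plausibly touched, along with the recorded sugammadex use and possibly per-protocol classification. Because sugammadex use and the TOF ratio at reversal are recorded, any reversal given at 0.9 or above would be visible in the data. The point is worth correcting because it is a conflicting instruction in patient care, not because it threatens the trial's main inference.

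**What to change.** Reconcile the two sentences under Anesthesia recovery stage so that a single rule covers a TOF ratio of at least 0.9 with clinical signs of residual block, and make the dose sentence consistent with that rule. The clinicians must decide which rule applies, and this review takes no position on it. Once the rule is settled, it will also be clear which action in this case counts as a deviation for the per-protocol analysis.

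The cost is a clarification of one or two sentences, with no additional patients, data or analysis.

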### Primary endpoint

The primary endpoint is the frequency of coughing episodes during FFB, calculated as the total number of coughing episodes divided by the procedure time. One coughing episode is defined as a period of continuous coughing that interferes with either adequate ventilation or procedural progress (1). Interference with ventilation is primarily identified by the main observer through real-time visual inspection of the capnography waveform and ventilator parameters. It is characterized by flattening or significant distortion of the capnography waveform for ≥3 s coincident with the cough or visible, sustained chest wall movement against the set ventilator cycle coincident with the cough. A concomitant decrease in SpO2 of ≥5% is a supportive but not mandatory criterion. Procedural interference refers to a situation where the bronchoscopist will verbally confirm any instance where coughing necessitates a deliberate pause in the advancement or manipulation of the bronchoscope to maintain visual clarity. A cough-free interval of at least 3 s between two consecutive coughs is considered as the criterion for distinguishing two separate coughing episodes.

Addressing the inherent challenge of precise chronometry during a dynamic procedure, the primary endpoint assessment will be conducted in real-time by a dedicated observer who is not engaged in other procedural tasks. This observer will receive training on the assessment protocol prior to the start of the trial to standardize recognition. The dedicated observer will also be trained to identify a distinct, perceptible pause in the coughing paroxysm, consistent with the approximate duration of 3 s, before recording a new episode. This method prioritizes clinical relevance and feasibility during an active procedure.

### Secondary endpoints

The secondary endpoints are: (1) cumulative remifentanil dosage; (2) success rate of FFB operation; (3) hemodynamic variables; (4) cough scores in the PACU every 5 min; (5) procedure time defined as the duration from bronchoscope insertion to its removal; (6) discharge time which is defined as the interval from the removal of bronchoscopy until a modified Aldrete score of ≥9 is achieved; (7) adverse events that occur during the procedure and in the PACU, including desaturation (SpO_2_ < 90%) which is stratified into three categories: mild desaturation: 85% ≤ SpO2 < 90%, moderate desaturation: 80% ≤ SpO2 < 85%, severe desaturation: SpO2 < 80%; laryngospasma; sore throat; bradycardia or hypotension defined as a decrease of at least 20% below the age-adjusted lower limit of heart rate or arterial blood pressure; tachycardia or hypertension defined as an increase of at least 20% above the age-adjusted upper limit of heart rate or arterial blood pressure; (8) satisfaction scores of bronchoscopists during the operation; (9) satisfaction scores of anesthesiologists; (10) satisfaction scores of parents 24 h after the operation. Given the age range of our study population (1–6 years), this score is reported as a proxy measure by the child’s parent or guardian, who is present throughout the preoperative, recovery, and immediate post-discharge periods. Satisfaction scores are measured subjectively by a simple numeric score between 1 (highly dissatisfied) and 10 (highly satisfied).

### Data collection and management

Demographic data include sex, age, weight, height, and BMI. Baseline characteristics encompass ASA physical status, as well as baseline values for HR, NIBP, SpO_2_, and baseline cough frequency (“occasional” or “frequent but stable”). Periprocedural data include the following: the total number of coughing episodes during the FFB intervention period; procedure time; cumulative remifentanil dosage; success rate of the FFB operation; HR, NIBP, SpO_2_, PetCO_2_, body temperature, BIS value, severity grading of pneumonia; the usage and dosage of sugammadex, the corresponding TOF ratio at the time of reversal; cough scores recorded in the PACU; discharge time; and adverse events that occurs during the procedure and in the PACU, including desaturation (SpO_2_ < 90%), laryngospasm, sore throat, bradycardia or hypotension, tachycardia or hypertension. Additionally, the data will capture anesthesiologist satisfaction, bronchoscopist satisfaction and parent satisfaction. All raw data will be meticulously documented in the Case Report Forms (CRFs) by an independent investigator. Upon completion of the trial for all patients, the principal investigator and the data administrator will jointly verify the integrity and accuracy of the data. Subsequently, the data administrator will import the verified data into a designated electronic database and forward it to a statistician for final statistical analysis.

#### Sample size

In a previous study by Tschiedel et al. comparing the use of propofol alone versus propofol combined with remifentanil during FFB, the addition of remifentanil resulted in a reduction of coughing episodes by approximately 60%, from 1.98 to 0.73 episodes per minute (1). Before implementing this trial, we prospectively studied 20 children undergoing FFB from April 2025 to May 2025. Our findings revealed that the frequency of cough episodes in children using the propofol-remifentanil regimen ranged from 0.6 to 0.89 episodes per minute, with a standard deviation (SD) of 0.3 episodes per minute, which is consistent with previously published data. Another 50% reduction in coughing episodes, decreasing the frequency to 0.3 episodes per minute with rocuronium, represents not only a statistically significant difference but also a clinically relevant improvement. We will require 64 subjects per group to achieve a power of 0.80 with a type I error rate of 0.05. Accounting for an anticipated dropout rate of 10%, the adjusted estimated sample size will be 70 children per group, resulting in a total of 140 children being randomized.

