The secondary endpoints will be analyzed using the multivariate logistic regression model or the generalized linear model, adjusting for the same covariates as those of the primary endpoint. Repeated measurement data will be analyzed using a mixed linear model to compare haemodynamic variables and cough scores in the PACU between groups. To address the issue of multiple comparisons for adverse events observed in secondary endpoints, the Benjamini-Hochberg procedure will be employed to control the false discovery rate.

The analysis will be performed on the modified intention-to-treat population. To ensure robustness, a per-protocol analysis will additionally be conducted; however, the intention-to-treat approach will remain the primary basis for analysis. Missing data will be processed by multiple imputation and maximum likelihood method. All endpoints are performed at the two-sided 5% significance level. Statistical analyses will be performed using SPSS statistics (version 19.0; IBM SPSS, Chicago, IL, USA).

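### The printed planning inputs lead to about 17 children per group, not 64; at 63 to 64 per group their power is above 0.999, so the sample size justification cannot be reproduced

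*Protocol article*

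**What the plan says.** All the planning figures stand in one paragraph, under Sample size.

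- **Pilot data.** The trial team studied 20 children. Under propofol and remifentanil the cough frequency "ranged from 0.6 to 0.89 episodes per minute, with a standard deviation (SD) of 0.3 episodes per minute".
- **Target.** "Another 50% reduction in coughing episodes, decreasing the frequency to 0.3 episodes per minute with rocuronium". A halving that ends at 0.3 implies a control rate of 0.6.
- **Result.** "We will require 64 subjects per group to achieve a power of 0.80 with a type I error rate of 0.05".
- **Dropout.** "Accounting for an anticipated dropout rate of 10%, the adjusted estimated sample size will be 70 children per group", which makes 140 in total.

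The Statistical analysis section adds the sidedness: "All endpoints are performed at the two-sided 5% significance level". It names Student's t-test for normally distributed continuous data and the Mann-Whitney test otherwise, with negative binomial or linear regression for covariate adjustment of the primary endpoint. The Sample size section itself names no test or formula, and it gives no dispersion parameter or smaller effect.

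**The concern.** The paragraph prints everything that a comparison of two means needs, and its answer does not follow from it. A difference equal to one SD needs a small trial, while 64 per group is the familiar answer for half an SD. Either the sample size or one of the inputs is misprinted, and a reader cannot tell which.

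What is at stake is the meaning of the stated power. If the printed inputs are right, 140 children aged 1 to 6 are randomized where about 38 would meet the stated aim, and the reason for the larger number is not given. If the SD used was really larger, the article misreports the variability on which the power rests. The pilot sentence, the only source for the SD, adds to the doubt because its interval and its SD do not fit together as labelled.

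**Working it through.** **Inputs.** Control rate 0.6, target rate 0.3 and SD 0.3 episodes per minute, power 0.80 and type I error 0.05 (Sample size); two-sided test (Statistical analysis); 1:1 allocation (Randomization and blinding).

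**1. What reproduces 64.** For two means, n per group is approximately 2 × (1.960 + 0.842)² / d² = 15.7 / d², where d is the difference divided by the SD. With d = 0.5 this is 62.8, and the exact t-test calculation gives 63.8, so 64 (power 0.801). A d of 0.5 means, for example, a difference of 0.3 with SD 0.6, or a difference of 0.15 with SD 0.3. The article prints neither pair.

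**2. What the printed inputs give.** d = (0.6 − 0.3) / 0.3 = 1.0. The approximation gives 15.7, so 16. The exact t-test calculation gives 16.7, so 17 per group (power 0.807 at 17). With 10% dropout, 17 / 0.9 = 18.9, so 19 per group and 38 in total. Power on these inputs is 0.9999 at 64 per group and 0.9998 at 63.

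**3. Other readings of the printed inputs (n per group).**
- Mann-Whitney test, relative efficiency 0.955 or 0.864: 18 or 20.
- One-sided 5%: 13 to 14.
- Power 0.90 or 0.95, t-test: 23 or 27.
- Control rate 0.73 (the published study) or 0.89 (the top of the pilot interval), with a target of 0.3 or half of control: 9 to 12, or 6 to 9.
- The largest value in any combination of these is 32 (Mann-Whitney at efficiency 0.864, power 0.95).

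**4. Count models.** For a log rate ratio, n = 7.849 × [1/(0.6t) + 1/(0.3t) + 2k] / (ln 2)², with t minutes observed and dispersion k.
- Negative binomial with assumed k = 2: 73.5 at t = 10 and 69.4 at t = 20. With k = 1: 40.8 and 36.8.
- Poisson (k = 0): 81.7 at t = 1 and 40.8 at t = 2.

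A count model therefore comes near 64 only with a large dispersion or one to two minutes of observation. The article gives neither.

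**5. Sensitivity to the SD (difference 0.3, 64 per group).** Power is 0.9999 at SD 0.3, 0.99 at 0.4, 0.92 at 0.5, 0.80 at 0.6 and 0.74 at 0.65.

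**6. Pilot sentence.** Values confined to an interval of width R have their largest sample SD when half lie at each end: (R/2) × √(n/(n − 1)). With R = 0.89 − 0.60 = 0.29 and n = 20, this is 0.145 × √(20/19) = 0.149. Even for two children it is 0.145 × √2 = 0.205. An SD of 0.3 is impossible for any number of children if the interval is their range.

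**7. Dropout.** 70 × 0.9 = 63 evaluable. Dividing, 64 / 0.9 = 71.1, so 72. Multiplying, 64 × 1.1 = 70.4, which is probably how 70 arose.

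**The case against.** The strongest reply is that nothing in the design is endangered. On the printed inputs the trial has ample power, the target is stated plainly as a 50% reduction, and planning from 0.6, the low end of the pilot interval, is cautious. All of that stands. It limits the point to a justification that cannot be reproduced; it does not rescue 64. Nor is this detail left to a fuller document, because the conflicting figures are printed side by side.

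A reader might also infer more than the article supports:

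- **That the trial is underpowered.** This would need an SD above about 0.6, or a difference below about 0.15 at SD 0.3. The article states neither.
- **That the real target was a 25% reduction.** That figure (0.15 / 0.6) appears only if the SD is held at 0.3 and the effect is solved for. An SD of 0.6 explains 64 equally well and leaves the 50% target intact.
- **That the pilot interval is a 95% confidence interval and the planned reduction is really 60%.** The half-width 2.093 × 0.3 / √20 = 0.140 does match, giving 0.605 to 0.885 around 0.745, and 1 − 0.3/0.745 = 60%. But 0.745 is simply the midpoint of the printed limits, and the calculation assumes that all 20 children had the propofol-remifentanil regimen, which the article does not say clearly. It remains an assumption.
- **That the dropout allowance is a second error of substance.** It is one child per group. Even at d = 0.5, power moves only from 0.801 to 0.795.

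**Conclusion.** The point holds as an error in the printed justification. The stated inputs give about 17 per group against 64, a 3.8-fold gap (64 / 17), and a power above 0.999 against the stated 0.80. On those inputs the error runs towards too many children. The result rests on a comparison of two means with a common SD of 0.3 and a control rate of 0.6, the only rate that fits both the 50% and the 0.3; the higher rates in the section need still fewer children. Separately, the pilot interval and SD are incompatible if the interval is a range. Which figure is wrong cannot be settled from the article, so the actual power for the 0.3 difference depends on an SD that the article does not establish. The paragraph needs correcting because it is the whole basis for the trial's size, but the correction concerns reporting and does not call for a different design.

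**What to change.** Keep 140 children and rewrite the Sample size paragraph:

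1. Report the pilot mean cough rate, the SD of the individual children's rates, and the number of children on the propofol-remifentanil regimen behind them.
2. Label 0.6 to 0.89 as what it is, whether a range, a confidence interval of the mean or something else.
3. State the test, control mean, SD and effect actually used to obtain 64.
4. If the printed inputs are the true ones, say that about 63 evaluable children per group give more than 99% power for 0.6 versus 0.3 at SD 0.3, and give the reason for the larger number. If another SD was used, print it with the power it gives.
5. Do not adopt a new target effect, such as a standardised difference of 0.5, to make 64 come out right. The 50% reduction is the stated target and should remain so.
6. As a minor correction, quote 63 rather than 64 evaluable per group after 10% dropout from 70.

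The cost is one reworded paragraph and a look back at the pilot data and the original calculation. No additional children are needed.
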